## Abstract

**Background:**

Treadmill training has been widely used for gait recovery after stroke. Gait re-establishment is one of the main objectives of rehabilitation programs after stroke, aiming to acquire more functional patterns and increase walking speed, along with improvement in cardiovascular function. The aim of this study is to evaluate the effects of a treadmill gait training protocol on functional and cardiovascular variables in patients with chronic stroke.

**Methods:**

A single-blind randomized clinical trial will be conducted. The sample will consist of 36 patients, who will be allocated in three groups: control group (n = 12), experimental group 1 (n = 12), and experimental group 2 (n = 12). The intervention will occur for 6 consecutive weeks, three times a week, 30 min each session, in all groups. The control group will perform a treadmill gait training without inclination, experimental group 1 will perform a treadmill gait training with anterior inclination of 5%, and experimental group 2 will perform a treadmill gait training with anterior inclination of 10%. All participants will be assessed for sample characterization measures, gait speed, functional capacity, systemic arterial blood pressure, heart rate, peripheral oxygen saturation, exercise capacity, neuromuscular torque, and quality of life. Evaluations of outcome measures will occur at the end of the interventions (post-training) and after 1 month and 1 year after the end of the interventions (short- and long-term follow-up). Statistical analysis will be performed descriptively and inferentially. Alpha equals 5% will be considered for inferential analysis. Mixed analysis of variance with repeated measures will be used to compare outcome measures between groups and between baseline, post-training, and follow-up. Normality test (Shapiro–Wilk) and subsequently *t* test (or Mann–Whitney) will be used to compare groups during the same training session.

**Discussion:**

It is believed that treadmill training, especially treadmill training with anterior inclination, may result in improved exercise capacity in patients with stroke, reduced blood pressure and heart rate values, and an improvement in functional parameters with increased gait speed, functional capacity, quadriceps muscle torque, and quality of life.

**Trial registration:**

Registration in Brazilian Registry of Clinical Trials (ReBEC) identifier RBR-5ffbxz, date of registration October 25 2017.

**Electronic supplementary material:**

The online version of this article (10.1186/s13063-019-3298-3) contains supplementary material, which is available to authorized users.

## Background

Stroke is an important cause of death and incapacity around the world, affecting about 795,000 individuals per year overall [1]. It is estimated that 75% of all deaths caused by stroke occur in developing countries, and 80% of individuals with disability after stroke are in these countries [2]. In Brazil, cerebrovascular diseases resulted in about 100,000 deaths in 2014 [3], and data indicate that about 568,000 affected individuals remain with severe disability [4].

People affected by stroke commonly present motor or sensory changes (or both), unilateral or bilateral, loss of strength and coordination, visual and cognitive impairments, and perceptual and language deficits [5]. These changes promote difficulties in executing functional activities and reduced performance of daily living activities and a consequent reduction in social participation which can aggravate the presented clinical situation [6].

An important factor leading to functional disability after stroke consists of gait deficits [7]. Hemiparetic gait is characterized by slow, laborious, and uncoordinated movement of limbs, although different gait patterns can be noticed according to the degree of motor recovery [8]. Since gait coordination is affected, the ability to change the walking pattern in response to environmental demands is also affected [9]. Therefore, other daily locomotion activities such as going up and down stairs, walking on sloped surfaces, and making turns and changing direction to return to a specific place or to avoid or go around obstacles are impaired as well.

Stroke patients who present hemiparetic gait have shown low levels of physical activity [10]. Physical inactivity leads to a decline in aerobic capacity, a decrease in exercise tolerance, and a limitation in daily activities [11]. Therefore, there is a vicious cycle involving physical inactivity and functional decline [12]. It is important to emphasize that increases in heart rate (HR) and systemic arterial blood pressure (BP) occur after stroke due to high sympathetic nervous system activity [13], and an increase is also associated with a decrease in physical fitness. In this way, gait recovery is one of the main objectives of stroke rehabilitation programs, which aim to acquire more functional patterns, increase walking speed, and improve cardiovascular function [14–16].

Studies have indicated that treadmill training improves gait speed [12, 17] and cardiovascular parameters, decreasing the BP and HR of these patients [13, 18], and it is more effective than conventional rehabilitation in improving aerobic capacity after stroke. In addition, treadmill training has been shown to be effective in improving postural balance, functional mobility, and lower limb function in patients with stroke [19–22].

Treadmill training can be carried out according to several protocols and also associated with difficult factors such as anterior or posterior inclination of the treadmill, direction changes in movement (backward), and an increase in load in order to increase weight [23–25]. Specifically, regarding the treadmill anterior inclination, some studies have been carried out in patients with stroke [20, 23, 26–28] given that walking on inclined surfaces is an activity commonly faced by community-dwelling people with locomotor impairments [26]. All of these studies observed improvement in gait variables—such as increased walking speed and range of motion of lower limbs, longer paretic step length, and improved gait balance and symmetry—during or after training on an inclined treadmill. Authors point out that slope seems to promote beneficial changes in hemiparetic gait pattern, which can lead to a better adaptation of ambulant stroke subjects to real environments [26, 27]. In addition to gait parameters, Globas et al. [20] investigated cardiovascular parameters after a fitness training (3 months), verifying better cardiovascular fitness with training on inclined treadmill compared with conventional physiotherapy. However, the degree of treadmill anterior inclination as a resistance grading in a fitness training (≥6 weeks) has not been investigated.

Thus, there is a strong need to design, implement, and evaluate training protocols which include functional activities—such as gait, walking up or down stairs, and ramps—to improve the cardiovascular condition of individuals with neurological pathologies, particularly stroke. Since treadmill training may influence functional and especially cardiovascular outcomes of individuals with a prior health condition, it is important to consider these variables in evaluating post-stroke training protocol effects. Also, Mehrholz *et al*. [29], in a recent systematic review, suggest further studies including different intensities (such as inclination) for treadmill training after stroke, as improved walking speed and endurance had no long-term benefits. In this context, the following questions arise: (1) Does inclined treadmill training promote cardiovascular and functional parameters in individuals with chronic stroke, and is it effective and safe for these patients when compared with treadmill training without inclination? (2) If inclined treadmill training promotes these parameters, what level of treadmill inclination is the most effective for improving cardiovascular and functional variables of individuals with chronic stroke?

The proposal of the study is to investigate whether treadmill inclination influences functional and cardiovascular parameters compared with treadmill gait without inclination and whether there are differences in effects on cardiovascular or functional parameters (or both) according to the degree of treadmill inclination during gait training.

## Methods/design

### Study setting and subjects

The present study is a single-blind randomized controlled clinical trial that follows the recommendations of the Consolidated Standards of Reporting Trials (CONSORT) [30].

Data collection procedures will be performed at the Laboratory of Intervention and Movement Analysis (LIAM), Department of Physical Therapy, Federal University of Rio Grande do Norte (UFRN), in the city of Natal, Rio Grande do Norte, Brazil.

The study population will consist of patients with stroke diagnosis who live in the city of Natal or nearby. Volunteer selection will be carried out in stroke patient care places, which may be public referral centers or private institutions of the city. The selection can also be carried out via spontaneous demand by the voluntary search of stroke patients after project advertisement on social media.

### Sample size

Sample size was calculated by using an online calculator [31], and the variable gait speed (in meters per second) was adopted as the primary outcome measure. According to a previous study involving individuals with post-stroke hemiparesis who performed treadmill training with partial weight support and anterior inclination of 10° (experimental) and no inclination (control) [26], standard deviations observed in the experimental and control groups were 0.1 and 0.2, respectively. The sample size was calculated from these data to detect a difference in gait speed between the groups of 0.18 m/s (α = 5% and power = 80%) since the minimum detectable difference in the gait speed for patients with chronic stroke was 0.18 m/s [32]. A ratio between the control and experimental groups of 1:2 was considered, as it was verified that the smallest numbers needed to detect the expected difference would be 8 individuals in the control group and 16 individuals in the experimental group, totaling 24 participants. Given a dropout rate of about 40%, a sample total of 36 participants (12 in the control group and 24 in the experimental group) was determined.

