### Randomization and blinding

Randomization sequence will be generated by computer [38], and three groups with blocks of 12 participants will be considered. This stage will be conducted by a researcher not involved in the study. This researcher will keep the randomization list confidential until the end of the study and will organize the allocation in sequentially numbered opaque envelopes. These envelopes will be sealed, and the randomization sequence will be according to the coding that will be created for study groups (control, experimental 1, and experimental 2).

The content of each envelope will be revealed only at the beginning of the training of each patient by study therapists in order to maintain allocation confidentiality. The same therapists involved in control group training will perform training in the experimental groups. Sample characterization measures and outcome measures will be evaluated by masked researchers in relation to group allocation. These researchers will be the same as those who enrolled participants in the study.

Only variables that will be collected during the training will be evaluated by study therapists (non-blind). Statistical analysis will be performed by one researcher, who will be blind to the allocation of patients in groups. Data will be tabulated with a predetermined encoding by another blinded evaluator, who will also check data (range check for data values). The present protocol has been prepared in accordance with relevant items from the SPIRIT (Standard Protocol Items: Recommendations for Interventional Trials) checklist (Additional file 1) and the SPIRIT figure (Fig. 1).

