## Statistical analysis

Data analysis will be carried out by a blinded evaluator regarding group allocation by using the Statistical Package for the Social Sciences software (SPSS, IBM, Armonk, NY, USA) for Windows. Only the main study researcher (not involved in data collection) can make the final decision to stop the trial and will have access to the final data.

Descriptive analysis of the sample characterization variables will be performed through central tendency and dispersion measures. Inferential analysis will consider statistical significance of 5% for all studied variables. Mixed analysis of variance (ANOVA) with repeated measures will be used to compare values and variations of outcome measures, comparing values between groups and between baseline, post-training, and follow-up assessments. Normality tests (Shapiro–Wilk) will be used for outcomes and will be compared between groups within each training session by using intergroup comparisons, *t* tests for independent samples, or Mann–Whitney tests.

Group description will be presented as mean and standard deviation, and the effect size and the 95% confidence interval will be reported. Intention-to-treat analysis will be performed for dropout data, considering the last data obtained from the participant.

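### The sample size covers one two-group 1:2 comparison with the inclined arms combined; the stated 80% power does not carry over to control versus a single inclined arm, and 5% versus 10% was not sized

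*Protocol article*

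**What the plan says.** The Sample size section takes gait speed as the primary outcome and sizes the trial "to detect a difference in gait speed between the groups of 0.18 m/s" with "α = 5% and power = 80"%. It does not say whether the test is one- or two-sided. From a previous study it takes the spread: "standard deviations observed in the experimental and control groups were 0.1 and 0.2, respectively". It then states: "A ratio between the control and experimental groups of 1:2 was considered", and arrives at "8 individuals in the control group and 16 individuals in the experimental group, totaling 24 participants". These numbers are raised to 12 and 24 for dropout.

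No single experimental group of 24 exists. The Abstract and the Randomization and blinding section describe control, 5% and 10% inclination as separate groups ("three groups with blocks of 12 participants will be considered"), 12 patients each.

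The Background asks two things: whether inclined training is better than flat training and, if so, "what level of treadmill inclination is the most effective for improving cardiovascular and functional variables of individuals with chronic stroke".

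The Statistical analysis section says: "Mixed analysis of variance (ANOVA) with repeated measures will be used to compare values and variations of outcome measures", between groups and across assessments, with t or Mann–Whitney tests between groups within training sessions. It names no contrast of the two inclined arms together against control.

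**The concern.** The 1:2 calculation can only mean that the two inclined arms count as one experimental group. That contrast suits the first research question, but the analysis does not name it. The second question needs the inclined arms kept apart, so the calculation cannot cover it.

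Two things are at stake. First, a reader will attach the 80% to whatever group comparison is reported, including control versus a single inclined arm, which has half as many experimental patients. Second, the Background presents the degree of inclination as the uninvestigated question. With no stated power for it, a non-significant 5% versus 10% result could be taken as showing that the slopes are equivalent.

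**Working it through.** **Inputs (Sample size section).** Difference d = 0.18 m/s; α = 5%, taken as two-sided (assumption); power 80%; SD 0.2 for control and 0.1 for experimental, as labelled. Evaluable: 8 and 16, that is 8 per arm once the 16 are split. Randomised: 12 per arm.

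**Step 1: reproduce 8 and 16.** With k = 2 experimental patients per control, n_control = (SD_c² + SD_e²/k)(1.96 + 0.84)²/d².
- As labelled: (0.04 + 0.005) × 7.849/0.0324 = 10.9, so 11 + 22 = 33. One-sided: 8.6, so 9 + 18 = 27. Neither gives 24.
- SDs swapped (control 0.1, experimental 0.2), two-sided: (0.01 + 0.02) × 7.849/0.0324 = 7.27, so 8 + 16 = 24, an exact match.
- A one-sided test with a common SD of 0.158 (root mean square of the two) also gives 8 + 16, but the protocol describes no such calculation.

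**Step 2: power of each contrast.** SE = √(SD₁²/n₁ + SD₂²/n₂). Normal power = Φ(d/SE − 1.96). The Welch figure uses the noncentral t distribution.

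| Contrast at 0.18 m/s | SE | Normal | Welch |
|---|---|---|---|
| Combined 8 v 16, SDs as labelled | √(0.04/8 + 0.01/16) = 0.0750 | 67% | 57% |
| Combined 8 v 16, SDs swapped | √(0.01/8 + 0.04/16) = 0.0612 | 84% | 80% |
| Combined 12 v 24, SDs as labelled | √(0.04/12 + 0.01/24) = 0.0612 | 84% | 78% |
| Control v one inclined arm, 8 v 8 | √(0.05/8) = 0.0791 | 62% | 54% |
| Control v one inclined arm, 12 v 12 | √(0.05/12) = 0.0645 | 79.6% | 74.5% |

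With equal arms, swapping the SDs does not change the last two rows.

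**Step 3: 5% versus 10%, 8 per arm.** The protocol gives no difference for this comparison. The range below uses the full 0.18 m/s and half of it (0.09, an assumption), with either SD.

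| Difference | SD in inclined arms | SE | Normal | Welch |
|---|---|---|---|---|
| 0.18 | 0.1 | 0.05 | 95% | 92% |
| 0.18 | 0.2 | 0.10 | 44% | 39% |
| 0.09 | 0.1 | 0.05 | 44% | 39% |
| 0.09 | 0.2 | 0.10 | 15% | 13% |

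The SD assignment that reproduces 8 and 16 is the one that puts 0.2 in the inclined arms.

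**Step 4: three-group test.** A simulated one-way ANOVA at a single time point, over both SD assignments and three mean patterns (0/0.18/0.18, 0/0.09/0.18, 0/0/0.18), has 40–72% power at 8 per arm and 60–91% at 12 per arm.

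**The case against.** **The calculation fits the first question.** That question is inclined versus flat, and the second is conditional on it. Sizing a small trial on its first question is defensible, and contrasts within an ANOVA are often left to an analysis plan that is not shown. This stands as a defence of the 1:2 choice. It does not make the 80% apply to other comparisons, and the protocol never says that the 80% is confined to the combined contrast.

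**Splitting the arms is not the main loss.** With the SDs as labelled, going from 8 v 16 to 8 v 8 lowers power only from 67% to 62% (57% to 54% by Welch). Most of the gap from 80% is already in the combined contrast. This stands. The split is costly (84% to 62%) only with the SDs swapped, so the fix must settle the SDs as well as the contrast.

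**Dropouts stay in the analysis.** The last available value is carried forward, so 12 per arm are analysed. This stands as to the count, but carried values can dilute the effect. If one third leave before post-training with no change recorded (assumption), 0.18 becomes 0.12 and power at 12 v 12 is about 46% (normal) or 42% (Welch).

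**The planned test is a repeated-measures ANOVA.** Its power depends on a within-patient correlation that the protocol does not give. The figures above are for single-time-point comparisons, as is the protocol's own calculation.

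**A stronger reading.** A reader might infer that no comparison in the trial has 80% power. The document does not support that. At 0.18 m/s with SD 0.1, 5% versus 10% has 95% or 92% at 8 per arm, although this needs the gap between slopes to equal the whole difference assumed for incline versus flat. Control versus one inclined arm is 79.6% by the normal formula with 12 evaluable per arm, and the three-group test exceeds 80% in some scenarios.

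**Conclusion.** The point holds in a limited form. The trial was sized for a two-group contrast that its analysis section does not name, and it gives no power for the between-slope question. At the plan's own 8 evaluable per arm, control versus one inclined arm has roughly 54–62% power, and it comes close to 80% only with 12 evaluable per arm, an undiluted effect and the normal formula. It would also be wrong to say that the combined contrast was powered at 80%: it was sized, but on the labelled SDs it has 57–67% at 8 v 16. For 5% versus 10%, the result could be anything from 13% to 95%, so no single power claim can be made. All figures assume a two-sided 5% test at one time point, with no multiplicity adjustment and no gain from repeated measures.

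**What to change.** 1. Name the combined inclined versus control contrast for gait speed at post-training as the primary comparison, because it is the one the calculation addresses.
2. Check in the source study which SD belongs to which group, state whether the test is one- or two-sided, and restate the power of that contrast.
3. Replace the blanket 80% with the power of control versus each inclined arm at 8 and at 12 per arm.
4. Report 5% versus 10% as an estimate with the 95% confidence interval that the Statistical analysis section already promises, and state that non-significance will not be read as equivalence.

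The cost is wording and one planned contrast, with no added patients. The downside is that the stated power will look less favourable and the second research question will be openly labelled as estimation.

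### The stated 80% power does not follow from the stated inputs: 8 + 16 is too few for the SDs given, and 36 randomised does not cover 40% dropout

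*Protocol article*

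**What the plan says.** The whole calculation is in the Protocol article, Methods/design, Sample size. Gait speed is the sizing outcome. From an earlier treadmill study, "standard deviations observed in the experimental and control groups were 0.1 and 0.2, respectively". The aim is "to detect a difference in gait speed between the groups of 0.18 m/s", with alpha 5% and power 80%. On allocation, "A ratio between the control and experimental groups of 1:2 was considered". The section says the size was computed from these data and that "the smallest numbers needed to detect the expected difference would be 8 individuals in the control group and 16 individuals in the experimental group", 24 in total. It then continues: "Given a dropout rate of about 40%, a sample total of 36 participants", made up of "12 in the control group and 24 in the experimental group".

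An online calculator is cited, but no formula, variance assumption or sidedness is given. Under Statistical analysis, dropouts are handled thus: "Intention-to-treat analysis will be performed for dropout data, considering the last data obtained from the participant".

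**The concern.** All the inputs and the result stand in one paragraph, and they do not agree. The control arm has the larger SD and is the smaller arm, so it dominates the standard error and should push the requirement up. The printed numbers look as though the larger SD had been attached to the larger arm. The dropout step then multiplies 24 by 1.5, which is not what a 40% loss requires.

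What is at stake is how the result will be read. The 0.18 m/s target is the section's own minimum detectable difference for gait speed in chronic stroke. If the trial finds no difference between inclined and level training, readers will take that as evidence from a study with 80% power. On its own inputs and its own dropout rate, the study has much less.

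**Working it through.** **Inputs (all from Sample size).** Control SD 0.2; experimental SD 0.1; difference 0.18 m/s; experimental to control ratio k = 2; alpha 5%; power 80%. Sidedness is not stated; two-sided is assumed and one-sided is also tried. As in the protocol, the comparison is control against the two inclined arms combined.

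**Formula.** For two means with separate variances, normal approximation:

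n(control) = (z₁₋α/₂ + z₁₋β)² × (SD_c² + SD_e²/k) / difference², with (1.96 + 0.8416)² = 7.849.

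**Reproducing the plan's 8 + 16.** It comes out with the SDs interchanged (control 0.1, experimental 0.2):

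7.849 × (0.01 + 0.04/2) / 0.0324 = 7.27, so 8 + 16 = 24. Power there is 84% (normal) or 80.2% (Welch t).

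**With the SDs as stated:**

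7.849 × (0.04 + 0.01/2) / 0.0324 = 7.849 × 0.045 / 0.0324 = 10.90, so 11 + 22 = 33.

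- A Welch t calculation needs 13 + 26 = 39.
- A one-sided test gives 8.59, so 9 + 18 = 27, still not 24.
- A simple averaged SD of 0.15 gives 8.18, so 9 + 18.

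**Power for 0.18 m/s with the stated SDs.** At 8/16, SE = √(0.04/8 + 0.01/16) = 0.075; 0.18/0.075 = 2.40; Φ(2.40 − 1.96) = 0.67. The other rows follow the same way:

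| Control / experimental with data | Normal | Welch t |
|---|---|---|
| 8 / 16 (the stated requirement) | 67% | 57% |
| 7 / 14 (36 randomised, 40% lost) | 61% | 50% |
| 12 / 24 (36 randomised, none lost) | 84% | 78% |

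Using the unrounded 7.2/14.4 instead of 7/14 gives 62% and 51%.

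**Detectable difference at 80% power (normal approximation).** At 8/16: 2.80 × 0.075 = 0.21 m/s. At 7/14: SE = √(0.04/7 + 0.01/14) = 0.080, so 2.80 × 0.080 = 0.22 m/s.

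**Dropout.**

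- Needed to keep 24: 24 / (1 − 0.40) = 40.
- Loss that 36 tolerates: 1 − 24/36 = 33%.
- Left after 40% loss of 36: 36 × 0.6 = 21.6, about 7 + 14.
- The common mistake of multiplying by 1.4 gives 33.6, so 34 in total. Applied to the control arm alone it gives 8 × 1.4 = 11.2, rounded up to 12. Doubling that gives 24, which may be where 12 + 24 came from.

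**The case against.** **An interchange is not the only route to 8 + 16.** This stands. Pooling the stated SDs with 1:2 weights gives √((0.04 + 2 × 0.01)/3) = 0.141, and 7.849 × 0.02 × 1.5 / 0.0324 = 7.27, hence 8 + 16 with nothing swapped. A one-sided calculation with the equally weighted pooled SD (0.158) also gives 8 + 16. The interchange is therefore a probable cause only. Neither route rescues the power claim, because the stated SDs differ twofold and the larger one sits in the smaller arm. In simulation with those SDs, an equal-variance t test at 8/16 rejects 77% of the time, but its true type I error is 11.6%, not 5%.

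**The protocol plans a mixed repeated-measures ANOVA, not a Welch test.** True, and its power depends on a within-patient correlation that the document does not give. But the sample-size paragraph itself makes a two-group comparison of means, and it has to be judged on that basis. The percentages should be reported with their method attached.

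**At 36 with full data, power is close to target.** Also true: 84% or 78%. But the same paragraph plans for about 40% loss. The protocol does not say at which visit that rate applies, so loss by the post-training visit could be smaller. Carrying the last value forward keeps 36 rows in the dataset but does not restore the missing outcome information.

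**The rate is only approximate.** The dropout error is indeed small in patients (21.6 left instead of 24), but 33% is not about 40%.

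**Conclusion.** The point holds. Under a separate-variance calculation the stated inputs require 11 + 22 (normal approximation) or 13 + 26 (Welch), not 8 + 16, and a one-sided test does not close the gap. Separately, 36 randomised does not protect 24 evaluable patients against 40% dropout; 40 would be needed.

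With the stated SDs and a test that holds its 5% level, power for 0.18 m/s is 57–67% at 8/16 and about 50–62% after 40% dropout. The difference detectable with 80% power after that dropout is about 0.22 m/s.

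This rests on the SDs being assigned as printed and on a two-sided comparison of control with the combined inclined arms. If the SDs turn out to be printed the wrong way round, 8 + 16 is right, but the dropout error remains: 7/14 would then give 78.5% (normal) or 74% (Welch), still under 80%. Why the authors arrived at 8 + 16 cannot be settled from the document.

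**What to change.** Rewrite the Sample size paragraph:

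1. Check the SD assignment against the source study, and state the formula, the variance assumption and the sidedness.
2. With the SDs as now printed, give the requirement as 11 control + 22 experimental evaluable, labelled as a two-sided normal approximation with separate variances (13 + 26 by Welch t).
3. Correct the dropout sentence: going from 36 to 24 is a 33% loss, and a 40% loss leaves about 21.
4. State what 36 randomised delivers for 0.18 m/s: about 50–62% power at 40% dropout, depending on method, or a detectable difference of about 0.22 m/s (normal approximation). With no dropout, power is 78–84%.

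The cost is wording only. Recruitment, conduct and analysis do not change. The price is a less favourable power statement, and a null gait-speed result should be interpreted against it.

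### The stated 80% power at 8 v 16 cannot be reproduced from the printed SDs, which give about 67% (normal) or 57% (Welch); the inputs need to be checked and stated exactly

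*Protocol article*

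**What the plan says.** The Sample size section takes gait speed as the sizing variable and draws its variability from a previous treadmill study: "standard deviations observed in the experimental and control groups were 0.1 and 0.2, respectively". The target is "to detect a difference in gait speed between the groups of 0.18 m/s", with "α = 5% and power = 80" per cent. On allocation it says "A ratio between the control and experimental groups of 1:2 was considered", and it concludes that "the smallest numbers needed to detect the expected difference would be 8 individuals in the control group and 16 individuals in the experimental group", 24 in total. Allowing for about 40% dropout, it sets enrolment at 36 (12 control, 24 experimental). The section cites an online calculator. It does not say whether the test is one- or two-sided, or whether the two SDs were entered separately or merged.

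Two statements under Statistical analysis bear on the consequences. The planned model is described as "Mixed analysis of variance (ANOVA) with repeated measures will be used to compare values and variations of outcome measures". For dropouts, "Intention-to-treat analysis will be performed for dropout data, considering the last data obtained from the participant".

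**The concern.** The article prints every main input to a two-mean sample size calculation, so its result should be reproducible. It is not. The smaller group (control) carries the larger printed SD, which is the unfavourable arrangement: the control mean then dominates the standard error, and 8 controls are too few for 80% power.

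A reader takes 24 completers as 80% assurance of detecting 0.18 m/s. If the SDs really are 0.20 (control) and 0.10 (experimental), the chance of missing that difference in the sizing comparison is 33% to 43% rather than 20%. If the labels were transposed in print, the size stands and only the text is wrong. If rounding hides a smaller control SD, the size may stand under the normal formula. The reader cannot tell these cases apart.

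**Working it through.** **Inputs (Sample size section).** Difference d = 0.18 m/s; control SD s_c = 0.2; experimental SD s_e = 0.1; control:experimental 1:2; alpha 5%; power 80%. Sidedness is not stated, so both are tried. The comparison is control v the two inclined arms combined.

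**Formulas.**
- SE = sqrt(s_c²/n_c + s_e²/n_e).
- Normal power = Φ(d/SE − z_alpha).
- Control group size at 1:2 = (s_c² + s_e²/2)(z_alpha + z_beta)²/d².
- Welch power uses the noncentral t with Satterthwaite df.

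**Attempt to reproduce 8+16 with the printed SDs, two-sided.**
- n_c = (0.04 + 0.005) × (1.960 + 0.842)²/0.0324 = 0.045 × 7.849/0.0324 = 10.90, so 11+22 = 33, not 8+16 = 24.
- At 8 v 16: SE = sqrt(0.04/8 + 0.01/16) = 0.0750 and d/SE = 2.40. Power is Φ(2.40 − 1.96) = 67.0% (normal) or 56.9% (Welch, df 8.8). A simulation of 400,000 trials gave 57.1% for Welch.
- Difference detectable with 80% power at 8 v 16: 2.802 × 0.0750 = 0.210 m/s (normal) or 0.237 m/s (Welch).

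| Size, printed SDs, two-sided | Normal | Welch |
|---|---|---|
| 8 v 16 | 67.0% | 56.9% |
| 11 v 22 | 80.4% | 73.7% |
| 12 v 24 | 83.6% | 77.9% |
| 13 v 26 | 86.4% | 81.6% |

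**One-sided 5%, printed SDs kept separate.** At 8 v 16, 77.5% (normal) or 71.4% (Welch). The smallest 1:2 sizes are 9+18 or 10+20.

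**Routes that do return 8+16.**
1. *SDs swapped* (control 0.1, experimental 0.2), two-sided: n_c = (0.01 + 0.02) × 7.849/0.0324 = 7.27, so 8+16. Power is 83.6% (normal) or 80.2% (Welch).
2. *One common SD.* Pooling by degrees of freedom gives sqrt((7×0.04 + 15×0.01)/22) = 0.140 and n_c = 7.10, so 8+16 two-sided (84.5% normal, 81.1% t). The simple average of the variances (SD 0.158) gives n_c = 9.08, so 10+20 two-sided; one-sided it gives 7.16, so 8+16. All of these assume equal variances, which the printed SDs contradict. With SDs of 0.2 and 0.1 at 8 v 16, the simulated two-sided pooled t test had about 76% power and a false-positive rate of about 11%, not 5%.
3. *Rounding.* The SDs are printed to one decimal, so a control SD of 0.2 covers roughly 0.15 to 0.25. With control 0.16 and experimental 0.10, n_c = (0.0256 + 0.005) × 7.849/0.0324 = 7.41, so 8+16, with 82.9% (normal) but 74.5% (Welch). Rounding also runs the other way: control 0.25 with experimental 0.10 gives 50% (normal) at 8 v 16.

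**The case against.** The strongest objection is rounding. With SDs given to one decimal, the printed labels can be right and 8+16 can still be the smallest 1:2 size under the ordinary normal formula, with no swap, pooling or mistake. That stands. It rules out calling the calculation proven wrong, and it rules out writing 67% or 57% into the protocol before the exact SDs are known. It does not make the text reproducible: the control SD must lie well below the printed 0.2, and the 0.16 example still falls short of 80% under Welch.

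A second objection is that a common SD reproduces the figure, and the article never says that the SDs were kept separate. As an account of what may have been typed into the calculator, this is fair. As a justification it fails, because a pooled test with the smaller group more variable does not hold its 5% level.

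A third is that the practical effect is limited, and this largely stands. Enrolment is 36. Carrying last values forward could bring up to 12 v 24 into the analysis (84% or 78% at exactly 0.20 and 0.10, before any dilution from carried-forward values). The mixed ANOVA uses baseline and may add power, although the article gives no baseline correlation. The 33% to 43% miss risk therefore belongs to the sizing comparison and not to the planned analysis.

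**Conclusion.** The point holds as a failure to reproduce. At the printed SDs, 8 v 16 gives about 67% (normal) or 57% (Welch) two-sided, and 80% at 1:2 needs 33 or 39 completers rather than 24. This assumes SDs of exactly 0.20 and 0.10, separate variances, normal data, and the two inclined arms combined against control.

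A reader might infer more, and the documents do not support it:
- *That the trial is shown to be underpowered.* The unrounded SDs are not given, and the planned mixed ANOVA is not the comparison calculated here.
- *That the SDs were certainly swapped.* A swap gives 8+16 neatly, but so do a common SD and a smaller unrounded control SD, and the article does not show what was entered.
- *That more patients are needed.* Nothing here establishes that.

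**What to change.** In the Sample size section, check the source study. State both SDs to two decimals with the group each belongs to, together with the sidedness and the formula used. Then recompute and restate the power for 0.18 m/s at 8 v 16 and at 12 v 24.

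- If the SDs are 0.20 (control) and 0.10 (experimental), state about 67% (normal) or 57% (Welch) at 8 v 16 and 84% or 78% at 12 v 24, and remove the claim that 8+16 are the smallest sufficient numbers. This applies even if a pooled SD was entered.
- If the labels were transposed, correct them and keep 8+16.
- If unrounded SDs explain the figure, print those SDs with the power they give.

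Say that these powers refer to the two-group comparison used for sizing. The cost is one check of the source study and one or two sentences. The only downside is a less favourable stated power if the first case applies. Enrolment does not change.
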